# Phase II/III multicentre randomised controlled trial evaluating a strategy of primary surgery and adjuvant chemotherapy versus peri-operative chemotherapy for resectable gastric signet ring cell adenocarcinomas – PRODIGE 19 – FFCD1103 – ADCI002

**DOI:** 10.1186/1471-2407-13-281

**Published:** 2013-06-10

**Keywords:** Signet ring cells, Gastric adenocarcinoma, Surgery, Perioperative chemotherapy, Randomized study, Emotion, Couple

## Abstract

**Background:**

A dramatic increase in the incidence of the diffuse form of gastric adenocarcinomas and particularly signet ring cell carcinomas has been observed in Western countries. Evidence is accruing that signet ring cell carcinomas may have inherent chemo resistance leaving many clinicians unsure of the benefits of delaying surgery to pursue a neoadjuvant approach.

**Methods/design:**

PRODIGE-19-FFCD1103-ADCI002 is a prospective multicentre controlled randomised phase II/III trial comparing current standard of care of perioperative chemotherapy (2x3 cycles of Epirubicin, cisplatin, 5-fluorouracil) with a strategy of primary surgery followed by adjuvant chemotherapy (6 cycles of Epirubicin, cisplatin, 5-fluorouracil) in patients with a stage IB-III gastric signet ring cell tumour. The principal objective of the phase II study (84 patients) is to determine if the experimental arm (primary surgery followed by adjuvant chemotherapy) has sufficient interest in terms of percentage of living patients at 24 months to be evaluated in a phase III trial. If 7 or less patients in the experimental arm are alive at 24 months, phase III will not be initiated. The primary objective of phase III (230 additional patients) is to demonstrate superiority of the experimental arm in terms of overall survival. Secondary endpoints include overall survival at 36 months, disease free survival at 24 and 36 months, R0 resection rates, treatment tolerance, postoperative mortality and morbidity evaluated by Clavien-Dindo severity index, the prognostic impact of positive peritoneal cytology and the assessment of quality of life. An ancillary study will assess the emotional and cognitive impact of surgery and perioperative chemotherapy for both the patient and their partner.

**Discussion:**

As inherent chemo resistance of signet ring cell tumours and delay in definitive surgery may favour tumour progression we hypothesise that a policy of primary surgery followed by adjuvant chemotherapy will improve overall survival compared to a standard perioperative chemotherapeutic strategy. This randomised phase II/III trial is the first dedicated to this histological subtype. Whilst the development of new biomarkers and targeted therapies are awaited, the results of this trial should further help in devising individualised protocols of patient care in a tumour group whose diversity increasingly demands assessment of alternative strategies.

**Trial registration:**

ClinicalTrials.gov, NCT01717924

## Background

Gastric adenocarcinoma (GA), despite its decreasing overall incidence, still remains the 5th most frequently diagnosed cancer and the second most common cause of cancer related death worldwide [1,2]. It is a heterogeneous disease with two histological classifications mainly being used. The Lauren classification [3] primarily differentiates between “intestinal” and “diffuse” types. The intestinal type corresponds to tubular or villous well-differentiated GA whereas the diffuse type corresponds to less differentiated and more infiltrative GA and includes signet ring cell adenocarcinomas (SRCs). As GA is typically a mixture of histological patterns, the World Health Organisation classification [4] has defined SRCs as an adenocarcinoma in which the predominant component (more than 50% of the tumour) consists of isolated or small groups of malignant cells containing intracytoplasmic mucins. A dramatic increase in the incidence of the diffuse form of gastric cancer and particularly SRCs has been observed, mainly in Western [5,6]. Consequently, in the most recent western studies, SRCs represents 16% to 45.4% of GAs [5,7,8].

The phase III trials [9,10] which have established peri-operative chemotherapy as the European standard of treatment for gastric cancers provide no subgroup analysis of the efficacy of this strategy for SRC tumours. A few retrospective [11-13] and prospective publications [14], with limited numbers of patients, have however suggested SRCs may have inherent chemo resistance. These observations have left many clinicians unsure of the benefits of delaying definitive surgery and pursuing a neoadjuvant approach for a tumour which behaves aggressively and displays significant resistance to current chemotherapy.

To support these observations and establish more reliable data regarding the behaviour of SRC tumours, at the start of 2010 our team launched a French retrospective multicenter study of all consecutive oesophagogastric adenocarcinomas in 19 centres in France treated between January 1997 and January 2010 (ADCI001) [8]. Amongst 3010 patients registered 1050 (34.9%) had a SRC tumour, with 126 being metastatic at diagnosis and excluded from the study. The remaining 924 patients underwent an intention to treat analysis according to whether they underwent primary surgery (n = 753, 81.5%) or neoadjuvant chemotherapy (n = 171, 18.5%). Multivariate analysis showed pre-operative chemotherapy to be an independent predictor of poor survival (HR = 1.4, 95% CI 1.1-1.9, p = 0.042), with overall survival at 2 years of 27.1% in the primary surgery group versus 12.3% in patients treated with neoadjuvant chemotherapy. Hence, increasingly data is suggestive of SRC chemo resistance, and a deleterious effect of delaying definitive surgery for an ineffective treatment whose toxicity may cause host immunosuppression facilitating disease progression.

There is therefore clear impetus for a prospective randomised study to evaluate the appropriate perioperative therapeutic strategy for SRCs.

## Methods/design

### Protocol overview

PRODIGE-19-FFCD1103-ADCI002 is a prospective multicentre controlled randomised phase II/III trial comparing current standard of care (2x3 cycles of perioperative Epirubicin, cisplatin, 5-fluorouracil (ECF) chemotherapy) with a strategy of primary surgery followed by adjuvant ECF chemotherapy (6 cycles) in patients with a SRC tumour and eligible for curative surgery. In phase II patients will be randomised using minimisation with stratification criteria – centre, tumour stage, performance status and tumour localisation. The principal objective will be to determine if the experimental arm (primary surgery followed by adjuvant chemotherapy) has a sufficient interest in terms of percentage of living patients at 24 months to be evaluated in a phase III trial. If ≤10% of patients in the experimental arm is alive at 24 months, phase III will not be initiated. Recruitment will be postponed for a 6 month period after the completion of phase II of the study to allow for the interim analysis of data. The primary objective of phase III will be to demonstrate the superiority of the experimental arm in terms of overall survival. The study is planned for a total duration of 10 years and is registered on clinicaltrial.gov website (NCT01717924).

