### Statistical evaluation and sample size calculation

Phase II– The phase II part of this trial will determine the percentage of patients in the experimental limb of the study (group B) who are alive at 24 months and thus validate the interest pursuing the evaluation of a strategy of primary surgery in a subsequent phase III trial. To demonstrate the interest of the experimental arm of this study, it will be necessary to include 40 in each treatment arm, with a unilateral alpha error of 5% and a power of 85%. Taking into account a 5% level of loss to follow-up, 84 patients will be included in total (42 in each treatment arm). If 7 or less patients are alive after 24 months, then the treatment B will be considered not interesting. Survival data for patients from phase II of this trial will allow for the readjustment of the number of patients required to be enrolled in the phase III trial according to the adaptive trial design.

Phase III – The objective of the phase III trial will be to demonstrate the superiority of group B and the principal outcome criteria will be overall survival. To demonstrate a desired 10% difference in overall survival in favour of group B at 24 months, with a bilateral alpha error of 5% and a power of 85%, it will be necessary to observe 291 deaths. With an estimated rate of inclusion of 6 patients per month, with a 5% rate of loss to follow-up and surveillance of the last included patient of 24 months, a total of 314 patients will have to be recruited. On this basis 230 additional patients will need to be recruited after the completion of phase II.

Two intermediate analyses are planned, one for Phase III sample size read justement and the second one to allow for the early identification of the superiority of group B. The first intermediate analysis of survival data will take place at the end of phase II. The second intermediate analysis will be performed after either 175 deaths or 60% of events have occurred.

Statistical analysis for phase II will be performed on a modified intention to treat population meaning all patients who can be evaluated and who are not lost to follow up at 24 months. For phase III, analysis of the main criteria will be performed on an intention to treat (ITT) principle. The per-protocol population will be defined as the ITT population having no major deviation or major of the protocol.

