Recently Messager et al [8] have published the results of a large multicentre comparative cohort study investigating the impact of peri-operative chemotherapy on survival in patients with SRC gastric tumours. It represents the largest study conducted on this histological subtype and involved analysis of 1050 patients diagnosed with SRC gastric tumours. No survival benefit was demonstrated for patients with SRC histology receiving peri-operative chemotherapy. Nor did neoadjuvant therapy result in tumour down-staging, down-staging of nodal disease, or decrease the disease recurrence. Indeed the authors found some evidence that disease progression during neoadjuvant treatment may have occurred in this subgroup of patients - extended resections were more commonly required and a longer median survival for patients treated with surgery alone prior to the incorporation of peri-oerative chemotherapy into the French guidelines for GA in 2006. This provides a clear imperative of the assessment of an alternative treatment strategy.

As several studies [11-14] have suggested a relative chemo resistance for SRC tumours and delay in definitive surgery may favour tumour progression [8] we hypothesise that a policy of primary surgery for SRC tumours, followed by adjuvant chemotherapy, will improve overall survival at 2 years when compared to a standard peri-operative chemotherapeutic strategy. This primary outcome criteria is justified as it provides a short term evaluation criteria (important in view of the very poor prognosis associated with this disease) and survival at 24 months has been found in a multicentre retrospective series of over 1000 patients to be significantly different (27% vs. 10%) [8].

This randomised trial will provide high level evidence regarding the value of a strategy of primary surgery for SRC gastric tumours. Whilst the development of new biomarkers and associated targeted therapies are awaited to individualise gastric cancer therapy, the results of this trial should will help further in devising individualised protocols of patient care in a tumour group whose diversity increasingly demands assessment of alternative strategies.

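### The phase II go/no-go rule is given as two different thresholds (≤10% alive, or 7 or fewer alive), so 5, 6 or 7 survivors lead to opposite decisions on opening phase III

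*Protocol article*

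**What the plan says.** The article states the phase II decision rule three times.

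- **Methods/design, Protocol overview:** "If ≤10% of patients in the experimental arm is alive at 24 months, phase III will not be initiated".
- **Abstract, Methods/design:** "If 7 or less patients in the experimental arm are alive at 24 months, phase III will not be initiated".
- **Statistical evaluation and sample size calculation:** "If 7 or less patients are alive after 24 months, then the treatment B will be considered not interesting".

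The statistical section ties its rule to a design of 40 patients per arm, a one-sided 5% error and 85% power. Enrolment is raised to 42 per arm (84 in total) for 5% loss to follow-up. The phase II analysis population is "all patients who can be evaluated and who are not lost to follow up at 24 months", so the denominator for group B is expected to be about 40 and can reach 42.

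No null rate or target rate is named as a design input. Two-year survival rates appear only as motivation. The Background reports "overall survival at 2 years of 27.1% in the primary surgery group versus 12.3% in patients treated with neoadjuvant chemotherapy"; the Discussion gives 27% versus 10% and cites the same retrospective series.

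**The concern.** The overview and the abstract attach the same consequence, not opening phase III, to different thresholds. Ten percent of 40 is 4 patients. Seven patients would be 10% only of an arm of 70, so neither rounding nor the choice between 40 and 42 as denominator brings the two together.

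This rule is the phase II primary decision, and it determines whether 230 further patients are recruited. Two people applying different parts of the article to the same 5, 6 or 7 survivors would reach opposite conclusions. The two versions would also carry very different risks of going forward with an uninteresting strategy, and only one of them can belong to a design stated at one-sided 5%.

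**Working it through.** **Inputs from the article.** n = 40 evaluable per arm (42 enrolled), one-sided error 5%, power 85%, no-go at 7 or fewer (abstract and statistical section), no-go at ≤10% (Protocol overview).

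**Assumed inputs.** The null rate p0 and target rate p1 are not stated. I use p0 = 10% and p1 = 26% for illustration and give the range for p0.

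**Step 1: put both rules on one scale.**

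| Evaluable in group B | ≤10% rule: no-go at | Count rule: no-go at | Count rule as a percentage |
|---|---|---|---|
| 40 | ≤4 (0.10 × 40 = 4.0) | ≤7 | 7/40 = 17.5% |
| 41 | ≤4 (0.10 × 41 = 4.1) | ≤7 | 7/41 = 17.1% |
| 42 | ≤4 (0.10 × 42 = 4.2) | ≤7 | 7/42 = 16.7% |

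The rules disagree at 5, 6 and 7 survivors in every row. This step needs no assumption about rates.

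**Step 2: reproduce the stated design.** Let X be the number of survivors, binomial(n, p), with phase III opened if X ≥ r. The error is P(X ≥ r | p0) and the power is P(X ≥ r | p1).

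- n = 40, p0 = 10%: P(X ≥ 7) = 0.0995 and P(X ≥ 8) = 0.0419. Eight is the smallest go count with error at or below 5%, so no-go at 7 or fewer is reproduced.
- p1 = 26%: P(X ≥ 8) = 0.853. With p0 = 10% and p1 = 26%, the smallest n reaching 85% power is exactly 40.

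**Step 3: how far the design fixes the null.** For 8 to be the smallest admissible go count at n = 40, we need P(X ≥ 8 | p0) ≤ 0.05 and P(X ≥ 7 | p0) > 0.05. The first holds up to p0 of about 10.4%, the second from about 8.5%. So p0 lies between roughly 8.5% and 10.4%.

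**Step 4: error of each rule over that range (n = 40).**

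| p0 | Count rule, P(X ≥ 8) | ≤10% rule, P(X ≥ 5) |
|---|---|---|
| 8.5% | 1.8% | 25% |
| 10% | 4.2% | 37.1% |
| 10.4% | about 5% | 40% |

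If all 42 are evaluable and p0 = 10%, the figures are 5.4% and 41.2%.

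**Step 5: chance of landing where the rules disagree.** P(5 ≤ X ≤ 7) = P(X ≥ 5) − P(X ≥ 8), n = 40.

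| True 24-month survival | P(5 to 7 survivors) |
|---|---|
| 10% | 0.371 − 0.042 = 33% |
| 15% | 49% |
| 20% | 0.924 − 0.563 = 36% |
| 26% | 0.989 − 0.853 = 14% |
| 27% | 0.992 − 0.883 = 11% |

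**The case against.** **The operative rule is clear enough.** The overview is a summary. The statistical section, where the rule stands beside its n, error and power, agrees with the abstract, and a trial statistician would work from there. The article also condenses a fuller protocol that is not shown, and that document may not contain the slip. This lowers the chance that the wrong rule is applied. It does not remove the contradiction in the text at hand.

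**The overview may mean the true rate.** Ten percent may be the uninteresting rate under the null hypothesis, written by mistake as an observed cut-off. That is the likeliest origin, but the sentence speaks of patients alive at 24 months and attaches an action, just as the abstract does. If a hypothesis was meant, the wording still has to change.

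**Both sentences could hold at once.** Each gives only a condition for not opening phase III, and 4 or fewer survivors satisfies both. But a reader takes a stated no-go threshold as the boundary of the decision, and nothing signals that a stricter one applies elsewhere.

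**The error rates rest on an inferred null.** This objection stands. A reader might infer that the design uses 10% against 26%, or that the trial runs at 37% error instead of 5%. The documents support neither as fact. The figure 26% appears nowhere; it is solved back from n = 40. The Discussion's pair, 10% and 27%, would give a smallest exact design of 34 patients with no-go at 6 or fewer (error 4.8%, power 85.1%). If the null were the Background's 12.3%, the count rule itself would have 11.1% error and the percentage rule 55.6%. The 37% is therefore conditional, and it applies only if the overview's sentence is the rule actually used.

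**Disagreement is less likely if the strategy works as hoped.** This is also true: 14% at 26% and 11% at 27%. The conflict matters most at the lower rates, where the go/no-go decision is hardest.

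**Conclusion.** The contradiction holds and needs no assumption: with 40 to 42 evaluable patients, 5, 6 or 7 survivors mean no phase III under the abstract and statistical section, and are not a no-go under the overview.

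The count rule is the one consistent with the stated n, error and power, provided the null is about 10%. Under that assumption, and over the 8.5% to 10.4% that the design allows, the overview's threshold read literally would have five or more times the intended 5% error. This identifies the overview sentence as the one to correct. It does not show that the phase II design is faulty or that the trial would be run on the looser threshold.

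The matter must be fixed because it concerns the rule that decides whether phase III opens, and because the conflict zone carries a probability of one third to one half when true survival is 10% to 20%.

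**What to change.** 1. In the Protocol overview, replace the ≤10% sentence with the rule from the statistical section: phase III is not opened if 7 or fewer of the 40 evaluable group B patients are alive at 24 months.
2. In the statistical section, have the sponsor state the null and target 24-month survival rates behind the 40 patients and the cut-off of 7. If 10% was meant as the null rate, say so, and say that it is not the observed cut-off. The rates should come from the sponsor's own calculation and not from the back-solved 26% used above.
3. If all 42 patients prove evaluable, report the exact error of the count rule (5.4% at a 10% null) and keep the cut-off. Raising it to 8 would bring the error down to 2.1% but would lower power to about 80% at an assumed 26% target, to remove an excess of 0.4 percentage points.

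The cost is one replaced sentence and one or two added ones. No patients, data or change to the sample size are involved.

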### Inclusion criteria

PRODIGE-19 will include patients with an adenocarcinoma of the stomach and Siewert type III tumours of the oesophago-gastric junction, with histological proof on pre-therapeutic biopsies of either a SRC tumour or diffuse type tumour according to the Lauren classification. Reliability of samples obtained from routine pre-treatment endoscopic biopsies to predict SRC histology has been recently demonstrated by our group [15].

All tumours of stage IB to III will be included (T1N+, T2N0 N+, T3N0 N+, T4N0 N+) as staged by routine endoscopic ultrasound examination (EUS), or by computerised tomography if the tumour is non-traversable at EUS. Patients will be between the ages of 18 and 80, must be assessed as suitable for curative surgery with the absence of visceral metastases or evidence of peritoneal carcinomatosis during a mandatory pretherapeutic staging laparoscopy. All included patients must have a weight loss of less ≤15% of body mass, have a World Health Organisation performance status of ≤2, with an ejection fraction of ≥50% prior to the administration of Epirubicin and must not have been previously treated with either chemotherapy or radiotherapy for a gastric cancer. Patients must have a neutrophil count of ≥1500/mm^3^, platelet count of ≥100,000/mm^3^, a creatinine clearance of >50ml/minute and a total Bilirubin <1.5 times the upper limit of normal. All patients must give their informed consent for participation in this trial.

### Exclusion criteria

All patients who do not meet the inclusion criteria will be excluded. Other contraindications to participation include tumours classified as T1N0 by preoperative staging, the presence of other malignant tumours treated with curative intent within 5 years (with the exception of basal cell carcinoma of the skin and carcinoma in situ of the cervix), patients previously treated with abdominal or thoracic radiation and patients with a known allergy to one of the trial medications. Current pregnancy or breastfeeding will render females ineligible. Evolving cardiac, renal and respiratory insufficiency, as well as myocardial infarction within 6 months and known Child’s B or C cirrhosis will all also warrant patient exclusion. Finally patients who are not capable for family, social, psychological or geographical reasons to attend for regular follow-up and who do not have legal capacity will not be included.

### Endpoints of trial

The primary endpoint of this trial will be the evaluation of the percentage of patients still alive 24 months after randomisation. The secondary endpoints for this trial include, overall survival (OS) at 36 months, disease free survival (DFS) at 24 and 36 months, R0 resection rates, treatment tolerance, postoperative mortality and morbidity evaluated by Clavien-Dindo severity index [16], rates of completion of all elements of the planned therapy, the prognostic impact of positive peritoneal cytology and the assessment of quality of life (EORTC QLC-C30 and EORTC STO 22). A complementary study, subsequently described, will assess the emotional and cognitive impact of surgery and perioperative chemotherapy for both the patient and their partner.

OS is defined as the time interval between inclusion and death from whatever cause and patients lost to follow-up will be censured at the last date of follow-up. Disease free survival will be defined as the time interval between the date of inclusion and the date of first recurrence or the date of death in the absence of disease recurrence. The R0 resection rate will correspond to the percentage of patients benefitting from a micro and macroscopically complete resection [17]. Neoadjuvant and/or adjuvant treatment tolerance will be estimated according to the National Cancer Institute Toxicity Criteria (NCI-CTC version 4.0). Evaluation of the uptake of all elements of planned treatment will be performed and quality of life questionnaires and human and social sciences questionnaires will be completed at 4 defined time-points – randomisation, the eve of commencement of treatment, 1 month (+/−7 days) after leaving hospital following surgery and 1 month (+/−7 days) after completing adjuvant chemotherapy. The quality of life questionnaires will also be completed at each 4 monthly follow-up visit.

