### Randomisation

Randomisation will be performed by minimisation with stratification criteria – centre, tumour stage, performance status and tumour localisation. The maximum delay between randomisation and either the start of neoadjuvant treatment or surgery will be 4 weeks. A randomisation number and the treatment allocation are sent by facsimile communication by the “Centre de Randomisation-Gestion-Analyse” (CRGA) at the Fédération Francophone de Cancérologie Digestive (FFCD) headquarters in Dijon, France to the investigator after the receipt of the inclusion form.

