### Pre-therapeutic work-up

Prior to inclusion in the trial an information booklet will be given to each patient and the trial protocol will be clearly explained. The initial work-up must take place in the 4 weeks preceding randomisation and will comprise of the following:

i) A complete physical examination.

ii) Estimation of full blood count, calculation of creatinine clearance using the Cockcroft formula, measurements of electrolytes, total protein, albumin, alkaline phosphatase, aspartate transaminase, alkaline transaminase, total and conjugated Bilirubin, gamma-GT, pregnancy test for females of reproductive years and discussion of contraceptive methods during the trial period.

iii) Tumour markers evaluation – carcinoembryonic antigen and carbohydrate antigen 19.9.

iv) Assessment of operability – electrocardiogram, cardiac echography, anaesthetic consultation and posterior-anterior and lateral chest x-ray (not necessary where a CT thorax has been performed).

v) Oesophago-gastro-duodenoscopy with multiple biopsies and examination by retroflexion.

vi) Contrast study.

vii) Contrast enhanced computerised tomography of the thorax, abdomen and pelvis.

viii) Endoscopic ultrasound will be performed systematically. The pre-therapeutic TNM classification will be made by EUS, except for tumours which cannot be traversed by EUS, in which case the TNM stage will be based on CT findings.

ix) Staging laparoscopy will be performed systematically. All suspicious lesions will be biopsied and a laparoscopic feeding jejunostomy will be performed for patients who have lost >10% of habitual body mass. Peritoneal fluid, if already present, will be sampled prior to any manipulation of the tumour and if the sample gives <50 mls, 100mls of normal saline will be instilled around the primary tumour and 50mls recuperated from the epigastric/left hypochondriac regions after a delay of 2 minutes without tumour manipulation. In cases of the discovery of peritoneal carcinomatosis, peritoneal cytology will not be performed.

x) Positron emission tomography scanning will not be routinely performed due to the known weak tracer uptake specific to SRC tumours [14].

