Continuous variables will be described by their mean and standard deviation or median, Interquartile Interval (Q1-Q3) and range. Survival endpoints will be estimated using the Kaplan Meier method, described by median values with 95% confidence Interval and compared in Phase III using the log-rank test. QoL data will be analysed according to treatment arm and treatment tolerance assessed using the National Cancer Institute Toxicity Criteria – (NCI CTC). The Clavien-Dindo scale will be used to assess peri-operative complications [16]. Cox univariate and multivariate analyses will allow exploratory analyses of prognostic factors, time until deterioration of QoL and disease free survival.

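### Phase III overall survival comparison leaves baseline peritoneal cytology unused, although it is sampled before randomisation and its prognostic impact is a named endpoint

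*Protocol article*

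**What the plan says.** All statements are in the protocol article.

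- **Endpoints of trial** (and the Abstract): the secondary endpoints include "the prognostic impact of positive peritoneal cytology".
- **Pre-therapeutic work-up**: "The initial work-up must take place in the 4 weeks preceding randomisation". Within that work-up, "Staging laparoscopy will be performed systematically", with peritoneal fluid or lavage taken for cytology. The one stated exception is: "In cases of the discovery of peritoneal carcinomatosis, peritoneal cytology will not be performed".
- **Inclusion criteria**: eligibility requires "absence of visceral metastases or evidence of peritoneal carcinomatosis during a mandatory pretherapeutic staging laparoscopy". The excepted patients are therefore not randomised. Positive cytology alone is not listed as an exclusion, so cytology-positive and cytology-negative patients can both enter.
- **Randomisation**: minimisation uses "centre, tumour stage, performance status and tumour localisation". Cytology is not among these.
- **Statistical evaluation and sample size calculation**: survival endpoints are "compared in Phase III using the log-rank test". No stratum or covariate is named, and Cox models are described as exploratory. Phase III is planned on a 10-point difference in overall survival at 24 months, two-sided 5%, 85% power, 291 deaths and 314 patients.
- **Surgical Resection**: cytology is taken again at resection, partly to study what preoperative chemotherapy does to it.

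**The concern.** The trial collects a baseline variable before allocation and considers its link with survival worth a named endpoint. It then compares survival between arms without using it. If the variable does predict survival, leaving it out of a log-rank test pulls the unadjusted treatment effect towards the null and gives up some power. A difference between arms in the share of cytology-positive patients would also remain in the estimate, because neither allocation nor the stated analysis addresses cytology.

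There is little slack elsewhere. The design needs 291 deaths from 314 patients (291/314 = 93%). With the planned 5% loss, about 298 patients remain (314 × 0.95), so longer follow-up can add few events. Baseline information is one of the few sources of precision that need no extra patients.

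**Working it through.** **1. The plan's own figure.** The sample-size text gives the 10-point difference but no control rate. I assume 10% versus 20% at 24 months; the 10% is the figure the Discussion quotes for the retrospective series.

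- HR = ln(0.20)/ln(0.10) = 0.699.
- Freedman: (1.960 + 1.036)² × [(1 + 0.699)/(1 − 0.699)]² = 286 deaths, within 3% of 291.
- Schoenfeld: 4 × (1.960 + 1.036)²/(ln 0.699)² = 280 deaths; power at 291 deaths is 86.3%.

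So 291 is consistent with 10% versus 20%. Starting from the 12.3% quoted in the Background, the requirement would be 322 (Schoenfeld) or 328 (Freedman).

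**2. Cost of omission with the within-stratum HR fixed at 0.699.** The documents give neither the prevalence of positive cytology nor its HR, so both are assumed over a range. Simulation: 314 patients 1:1, accrual over 52 months (about 6 per month), exponential survival, control survival 10% at 24 months, analysis at 291 deaths, 8000 replicates (Monte Carlo standard error about 0.4 points).

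| Prevalence | Cytology HR | Plain log-rank | Stratified | Gain (points) |
|---|---|---|---|---|
| 5% | 2 | 84.6% | 85.1% | 0.5 |
| 10% | 1.5 | 85.5% | 85.7% | 0.2 |
| 10% | 2 | 84.4% | 85.6% | 1.2 |
| 10% | 3 | 83.0% | 85.7% | 2.7 |
| 20% | 1.5 | 84.8% | 85.7% | 0.9 |
| 20% | 2 | 82.8% | 85.6% | 2.8 |
| 20% | 3 | 78.8% | 85.3% | 6.5 |
| 30% | 2 | 81.8% | 85.9% | 4.1 |
| 30% | 3 | 75.6% | 84.9% | 9.3 |

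**3. The same comparison with marginal survival held at the planned difference.** Fixing the within-stratum HR makes the overall difference smaller than 10 points. For prevalence 20% and HR 2, let u be 24-month control survival in cytology-negative patients: 0.8u + 0.2u² = 0.10 gives u = 0.1213. In group B, u^0.699 = 0.229, and 0.8 × 0.229 + 0.2 × 0.229² = 19.4%, not 20%. To reach 20%, 0.8v + 0.2v² = 0.20 gives v = 0.2361, so the within-stratum HR must be ln(0.2361)/ln(0.1213) = 0.684. Group B survival in step 2 is 18.9% at 20% with HR 3, and 18.4% at 30% with HR 3.

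With marginals held at 10% versus 20% (3000 replicates):

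| Prevalence | Cytology HR | Plain log-rank | Gain from stratifying (points) |
|---|---|---|---|
| 10% | 1.5 | 85.2% | 0.4 |
| 20% | 2 | 86.7% | 2.2 |
| 20% | 3 | 86.5% | 4.1 |
| 30% | 3 | 86.3% | 7.5 |

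The plain test meets 85% in each scenario. The gain from stratifying comes on top of that.

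**4. Validity and imbalance.** With a treatment HR of 1, two-sided type I error is 5.0% to 5.5% for both tests. The standard deviation of the chance between-arm difference in cytology-positive share is √[2q(1 − q)/157]: 2.5 points at q = 5% and 5.2 points at q = 30%.

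**The case against.** The strongest objection is that nothing in the article is wrong or contradictory. Covariate lists usually sit in a statistical analysis plan, which is not shown, and the exploratory Cox models could include cytology. This limits the point to an efficiency recommendation. It does not remove it, because the article states its method (a log-rank test with no stratum, Cox models as exploratory) and that stated method can be improved with data already collected.

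Four stronger readings are tempting, and the documents do not support them.

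- *The sponsor already regards cytology as an established prognostic factor.* The endpoint is a question to be answered; no section says the answer is known.
- *Phase III is underpowered because cytology is omitted.* The plan is framed as a marginal difference at 24 months. Held at 10% versus 20%, the plain test reaches 85%. The lower figures in step 2 arise partly because that set-up shrinks the marginal benefit.
- *Chance imbalance biases or invalidates the comparison.* Randomisation allows for it, and type I error is about 5% either way. What remains is a possible imbalance in the one trial actually run.
- *Cytology should have been a minimisation factor.* The article fixes when the sample is taken, not when the result is available, so it does not show that the result could have been used for allocation.

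The objection that the larger gains need a cytology HR of 3 in a population already screened to exclude carcinomatosis also stands as a caution: no section supports or rules out such values.

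**Conclusion.** The point holds as a missed gain in precision, not as an error. Baseline cytology should be available for essentially all randomised patients, is not balanced by minimisation and does not enter the stated phase III comparison. The test is valid, and the planned power is met under the assumed 10% versus 20%.

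The size depends wholly on an assumed prevalence and HR. The gain is under 1 to about 3 points of power for prevalence up to 20% and HR up to 2. It is about 4 to 9 points for prevalence 20 to 30% with HR 3, and 30% with HR 2 sits at the lower end of that range. Apart from simulation noise at the weakest settings, stratifying did no harm in these scenarios.

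**What to change.** In the statistical section, and in the analysis plan if it does not already do so, pre-specify the phase III overall survival comparison as stratified by, or adjusted for, cytology from the staging laparoscopy, in three categories: positive, negative, not available. Use only the pre-randomisation sample. The resection sample must never serve as the covariate, because in group A it is taken after chemotherapy and can be affected by treatment. Report the cytology split by arm with the baseline data.

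The cost is a change of wording, made before any comparison by arm. The result is already collected and minimisation stays as it is. The small downside is carrying a category for samples that were inadequate or missing.
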